#### Distal outcomes

For the distal outcomes (PHQ-9, MHC-SF, QPR, and EQ-5D), propensity score matching will be used to match participants in the TAU group with those in the TAU + JITAI group. Propensity scores are calculated via logistic regression analysis [38], which models the probability of receiving treatment (TAU + JITAIs versus TAU) as a function of baseline covariates, including sex, age, and severity of depressive symptoms at the start of treatment. After the propensity scores are calculated, participants from the TAU group are matched with participants from the TAU + JITAIs group via a matching method (nearest neighbor matching with a caliper). This method ensures that each participant in the TAU + JITAIs group has a corresponding participant in the TAU group with a similar propensity score, making the groups similar in terms of the matched covariates. The matched sample is then used in a mixed-effects model that considers the paired nature of the matched sample by including the matched pairs as random effects. This ensures the correct estimation of standard errors and appropriate interpretation of the results. The fixed effects in the model include time (baseline, 1-week and 6-week assessment), group status (TAU + JITAIs versus TAU), and their interaction, whereas the random effects model includes variability between matched pairs and within individual participants over time. A significant interaction suggests that changes in the outcomes (PHQ-9, MHC-SF, QPR, and EQ-5D) differ between groups.

Participants may pause or discontinue the JITAI component at their own request, at the advice of the treating clinician. Data collected until then will be used for analyses, and participants will be asked to complete the outcome questionnaires. This will not affect access to TAU, and no protocol-driven modification of TAU is planned. Possible harms are expected to be limited and may include burden, annoyance, or temporary distress related to EMA or prompts. Any adverse events will be documented and discussed with the treating clinician.

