They will complete baseline questionnaires (PHQ-9, MHC-SF, QPR, and EQ-5D) and undergo a 1-week baseline period with two EMA surveys per day following a semi-random sampling in time blocks of 1 h (e.g., 09:00–10:00; 12:00–13:00; 15:00–16:00, and 18:00–19:00). Each assessment takes place at random moments in one of the time blocks, and scheduling of the time blocks is decided by the participants at the start of the baseline. After the baseline period, the intervention phase (MRT) will start and last 6 weeks. During the MRT, participants receive four EMA surveys per day—following semi-random sampling in time blocks of 1 h—which serve as a decision point. At each decision point, the participant is eligible for randomization if they (1) completed the EMA and (2) met a prespecified tailoring-variable threshold indicating that they are in the symptomatic half of the item scale (i.e., a vulnerability state for withdrawal/avoidance). Because the EMA includes both negatively and positively valenced items, thresholds are operationalized in a directionally consistent way: for negatively valenced symptom items (e.g., “I feel down,” “I feel tired,” “I feel listless”), eligibility is defined as a score ≥ 4; for positively valenced functioning items (e.g., “I feel energetic”), eligibility is defined as a score ≤ 4. This threshold was selected to identify "moderate-or-worse" vulnerability states where the risk of avoidance is elevated [35] while managing participant burden by preventing prompting during mild or asymptomatic states. If the decision point is eligible for randomization, there is a 50% probability of receiving a JITAI and a 50% probability of receiving no JITAI. Thus, randomization occurs repeatedly within participants across eligible decision points. Allocation to the TAU + JITAI and TAU groups is not randomized. Within the TAU + JITAI condition, randomization at eligible decision points is generated automatically by m-path (simple randomization), and recruiters do not have access to future assignments. Because of the nature of the intervention, participants, therapists, and researchers are not blinded to study condition; therefore, no formal blinding or unblinding procedures apply.

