For each participant, the tailoring variables will represent (1) one of the EMA items assessing depressive symptoms that exhibited the highest average score during their baseline period, and (2) one of the EMA items assessing depressive symptoms that the participant rated as “most impactful” on their daily functioning identified via a shared decision-making procedure following the baseline week. Specifically, a researcher and the participant jointly review visualized baseline EMA data (e.g., timeline plots of the symptom items), and the participant identifies which symptom most hindered their daily functioning and/or engagement in planned activities. This self-identified symptom is operationalized as the “impactful” tailoring variable. At the end of each study day, participants will receive an EMA survey that does not serve as a decision point. Two questions are added to the evening survey (activity level and best moment of the day). Importantly, the JITAIs are embedded in a therapist-supported treatment. During weekly therapy sessions, the EMA data collected during the week are visualized (e.g., timeline plots of mood and activities) and reviewed collaboratively by the therapist and participant. This integration aims to support engagement. The questionnaires completed at baseline (PHQ-9, MHC-SF, QPR, and EQ-5D) will be administered again at the start of the JITAI phase and at the end of treatment. In addition, at the end of treatment, participants will complete questionnaires regarding the acceptance of the JITAIs (CSQ-8, SUS, TWEETS). Participants in the TAU group will complete these questionnaires (PHQ-9, MHC-SF, QPR, EQ-5D) at the same time points. Participating patients in the TAU + JITAI group will receive a remuneration of 25 euros when they have completed the questionnaires at the last time point. Therapists will be interviewed at the end of treatment to share their experiences with patients using JITAIs.

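### In the nonrandomised distal comparison, baseline MHC-SF, QPR and EQ-5D are not named for matching and no outcome is adjusted for its own baseline; a baseline-adjusted estimate should stand beside the change contrast

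*Protocol article*

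**What the plan says.** The two groups are not formed by chance: "Allocation to the TAU + JITAI and TAU groups is not randomized" (Procedure, Evaluation phase). For the TAU + JITAI group the same section says "They will complete baseline questionnaires (PHQ-9, MHC-SF, QPR, and EQ-5D", and later "The questionnaires completed at baseline (PHQ-9, MHC-SF, QPR, and EQ-5D) will be administered again at the start of the JITAI phase"; a third administration follows when treatment ends. For the comparator it says "Participants in the TAU group will complete these questionnaires (PHQ-9, MHC-SF, QPR, EQ-5D) at the same time points". Table 2 agrees. All four distal scales are thus measured in both groups on two occasions before any JITAI is delivered and once at the end.

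Under Data analyses, Distal outcomes, the propensity score is modelled "as a function of baseline covariates, including sex, age, and severity of depressive symptoms at the start of treatment". Nearest-neighbour matching with a caliper follows. The outcome model is then given: "The fixed effects in the model include time (baseline, 1-week and 6-week assessment), group status (TAU + JITAIs versus TAU), and their interaction". The "random effects model includes variability between matched pairs and within individual participants over time". The test is read as follows: "A significant interaction suggests that changes in the outcomes (PHQ-9, MHC-SF, QPR, and EQ-5D) differ between groups".

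The Sample size section gives no power or precision for these outcomes and calls their estimates preliminary. The Discussion accepts a raised risk of Type II error in the between-group comparison.

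**The concern.** Hypothesis 3 covers depression, well-being, personal recovery and quality of life. The matching names the baseline construct of the first only. If severity of depressive symptoms means the PHQ-9, one of the four outcomes is analysed after balancing its starting value, while the other three are analysed without any stated attempt to do so. No reason is given for the difference.

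The outcome model does not make up for this. Baseline enters as one level of the response, not as a covariate, so none of the four outcomes is conditioned on its own starting value.

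Two things are at stake. Precision is given up in a comparison that the article already regards as likely to be too small. In addition, groups that were not randomised may start apart on MHC-SF, QPR or EQ-5D, and part of that gap can appear as a difference in change. These estimates are meant to inform a later trial.

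**Working it through.** **Inputs.** From the article: three assessments per scale, nonrandomised groups, the named propensity covariates, the fixed and random effects, and 46 participants per group after dropout. The 46 comes from the adherence calculation, which reproduces: design effect 1 + 27 × 0.05 = 2.35; half-width 1.96 × √(0.6 × 0.4 × 2.35 / (46 × 28)) = 0.041. That figure concerns feasibility; there is no distal figure to reproduce. Assumed, because the article gives none: the correlation ρ between assessments, equal variances (outcomes in SD units), and the size of any baseline gap.

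**Step 1: what the interaction estimates.** The described model was fitted to simulated complete data with matched-pair and participant random effects. The baseline-to-6-week interaction and the raw difference in mean change were both −0.3955. The contrast is a difference in raw change, and a constant gap cancels.

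**Step 2: precision against a single-baseline change contrast.** Residual variance is 2(1−ρ) for change and 1−ρ² with baseline as covariate; their ratio is 2/(1+ρ). The standard error is √(2v/46), and the difference detectable with 80% power is 2.80 × SE.

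| ρ | v, change | v, adjusted | ratio | SE, change | SE, adjusted | detectable, change | detectable, adjusted |
|---|---|---|---|---|---|---|---|
| 0.3 | 1.40 | 0.91 | 1.54 | 0.247 | 0.199 | 0.69 | 0.56 |
| 0.5 | 1.00 | 0.75 | 1.33 | 0.209 | 0.181 | 0.58 | 0.51 |
| 0.6 | 0.80 | 0.64 | 1.25 | 0.187 | 0.167 | 0.52 | 0.47 |
| 0.8 | 0.40 | 0.36 | 1.11 | 0.132 | 0.125 | 0.37 | 0.35 |

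**Step 3: the second pre-intervention score.** The article does not say which interaction contrast is read. If it is change from the mean of the two pre-intervention scores, and all pairs of assessments correlate ρ, the variance is 1.5(1−ρ): 1.05, 0.75 and 0.45 at ρ = 0.3, 0.5 and 0.7. Adjusting for baseline alone gives 0.91, 0.75 and 0.51, so the gain vanishes at 0.5 and reverses at 0.7. Adjusting for both pre-intervention scores gives 1 − 2ρ²/(1+ρ) = 0.86, 0.67 and 0.42. A gain remains, but a smaller one (ratios 1.22, 1.13 and 1.06).

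**Step 4: imbalance and bias.** Matching on sex, age and PHQ-9 was simulated with 46 per group, a caliper of 0.2 SD of the logit and a correlation of size 0.5 between PHQ-9 and the outcome (all but the 46 assumed; 1,500 repetitions). About 34 to 35 pairs remained. A 0.3 SD gap in the baseline of another outcome stayed at about 0.3 SD after matching. Adding that baseline to the propensity model brought the mean gap to about 0.

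How such a gap affects the estimate depends on the mechanism (true effect zero, 0.3 SD gap):

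| Mechanism | ρ | change contrast | baseline-adjusted |
|---|---|---|---|
| follow-up depends on observed baseline | 0.4 | −0.184 | −0.002 |
| | 0.6 | −0.125 | −0.001 |
| | 0.8 | −0.058 | 0.000 |
| gap stable over time | 0.4 | −0.002 | +0.183 |
| | 0.6 | +0.004 | +0.124 |
| | 0.8 | −0.001 | +0.056 |

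The non-zero entries follow (1−ρ) × 0.3: 0.18, 0.12 and 0.06. At ρ = 0.5 the same product is 0.15 SD.

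**The case against.** The strongest reply is that change from baseline is the question the article asks, and that without randomisation neither change nor baseline adjustment is safe by default. Each rests on an assumption the data cannot settle, and nothing in the article says which is nearer the truth. This stands. A reader might infer that the planned interaction is biased and should be replaced by a baseline-adjusted model. The documents do not support that: under a stable gap the replacement would bring in an error of the same size.

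Three other tempting readings also go too far.

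- That the three baseline scores are excluded from the matching. The covariate list is introduced as open, and an article may condense a fuller list. All that can be said is that they are not named.
- That baseline is ignored in the model. It is a response level, and a constant gap is subtracted.
- That chance imbalance on these scores is a bias on top of the precision loss. It averages to zero and is already contained in the variance 2(1−ρ).

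The reply does not dispose of the point. The plan already conditions on starting depressive severity, so it has accepted conditioning for one outcome without explaining why the other three differ. The open list does not help the outcome model either, whose stated fixed effects include no baseline score.

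**Conclusion.** The point holds in a limited form. Baseline MHC-SF, QPR and EQ-5D are not named as matching variables, and none of the four distal outcomes is adjusted for its own baseline in the outcome model. The precision loss therefore applies to PHQ-9 as well. It amounts to 11% to 54% more variance for assumed ρ of 0.8 to 0.3, if the contrast uses a single baseline. It is smaller if both pre-intervention scores are averaged, and absent or reversed in places if the adjustment then uses baseline alone.

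The bias is conditional. It is (1−ρ) times the residual imbalance if follow-up depends on the observed baseline, and nil if the group gap is stable. All sizes rest on assumed correlations and gaps. The consequence is modest: the primary outcome is feasibility, no progression criterion uses these scales, and the article treats the distal estimates as preliminary. It is worth changing because the data are already collected.

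**What to change.** In the Distal outcomes section:

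1. Name baseline MHC-SF, QPR and EQ-5D in the propensity model alongside depressive severity.
2. For all four distal outcomes, report a baseline-adjusted group difference at the end of treatment beside the planned change contrast. Use both pre-intervention scores as covariates and keep the matched-pair random effect. State which interaction contrast is read.
3. State the assumption behind each estimate: that follow-up depends on the observed baseline, or that the group gap would have stayed constant.

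One consequence should be made explicit. Once the baseline scores are in the matching, the change contrast in that sample also conditions on them. In the stable-gap simulation it was then off by +0.185, +0.128 and +0.056 SD at ρ = 0.4, 0.6 and 0.8. If the change contrast is to represent the stable-gap assumption, it should also be shown in the sample matched on the covariates now named.

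The cost is wording, one or two more parameters per model, and possibly a few more participants outside the caliper. No new data are needed. An adjusted model of the final score alone also drops participants who lack it, which is a further reason to keep the planned repeated-measures analysis beside it.

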## Background

Depression is a major public health problem, with a rising prevalence and negative impact on quality of life, mortality, and morbidity [1]. Several effective treatments are available, including medication and psychological treatments. Although treatments are effective, they appear to be effective for only approximately half of the participants [2, 3]. These findings indicate that further research is needed to improve the treatment of depression.

Behavioral activation is one of the recommended psychological treatments for depression. While it is the behavioral component of cognitive behavioral therapy (CBT), it has also developed into a stand-alone treatment that can be as effective as the full CBT package [4, 5]. Behavioral activation encourages individuals with depression to seek activities that are expected to result in a sense of pleasure, mastery, or accomplishment. Examples of behavioral activities include gardening, walking, swimming, watching TV, cooking a favorite meal, reading a book, and talking about sports. Strategies such as monitoring mood, identifying pleasurable activities, and planning activities are used to achieve this goal. Meta-analyses have shown a large effect of behavioral activation on depressive symptoms [6], and several studies have shown that behavioral activation can be effectively implemented by a variety of trained disciplines [7–9].

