### Participants

#### Participants with depression

Participants will be recruited from a mental health institution in the Netherlands. For the design phase, a purposive sample of twelve participants with depression, including six participants with low literacy or low digital literacy, will be recruited. For the evaluation phase, 104 participants will be recruited: 52 for the treatment-as-usual with the JITAIs as add-on condition (TAU + JITAIs) and 52 for the treatment-as-usual (TAU) condition. The inclusion criteria for the participants in the evaluation phase are as follows: (a) age 18 years or older, (b) diagnosis of depressive disorder according to the DSM-5, (c) scheduled to start (cognitive) behavioral therapy for depression and (d) possession of an Android or iOS smartphone. The exclusion criterion is insufficient proficiency in Dutch to participate in the study and complete the questionnaires.

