#### Therapists

The participating therapists will be recruited from the same mental health institution as the participants. Therapists include nurses, nurse practitioners, master-level psychologists, registered psychologists, or psychiatrists.

For the design phase, 4 therapists from different disciplines will be recruited. For the evaluation phase, 10 therapists will be recruited. In the evaluation phase, all participating therapists will attend a 2-h workshop explaining the JITAIs and the software application used for the JITAIs. At the end of the study, the therapists will be asked to discuss how they and their patients have experienced the JITAIs through a qualitative interview and a questionnaire [22].

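### None of the covariates named for the propensity score concerns background treatment, so an imbalance in antidepressant use between the nonrandomised arms could appear as a JITAI effect

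*Protocol article*

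**What the plan says.** The protocol article states under Procedure, Evaluation phase: "Allocation to the TAU + JITAI and TAU groups is not randomized". Under Data analyses, Distal outcomes, the probability of being in the JITAI arm is modelled from baseline covariates, "including sex, age, and severity of depressive symptoms at the start of treatment". TAU participants are then matched to JITAI participants by "nearest neighbor matching with a caliper", which the plan describes as "making the groups similar in terms of the matched covariates". The outcome model has fixed effects for time, group and time by group, with random effects for matched pair and for participant. A significant interaction is read as a difference in change between groups.

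On background treatment:

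- Eligibility (Participants with depression) requires that patients are "scheduled to start (cognitive) behavioral therapy for depression".
- On who delivers it, the Therapists section says: "Therapists include nurses, nurse practitioners, master-level psychologists, registered psychologists, or psychiatrists".
- The Distal outcomes section adds that the protocol will not alter TAU.
- Medication appears once, in the Background: "Several effective treatments are available, including medication and psychological treatments". No eligibility criterion, listed measure or named covariate refers to it.

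The comparison serves the third hypothesis (Study aims and hypotheses), that distal outcomes improve more with JITAIs than with TAU. The Sample size section calls the distal results preliminary input for a later trial. The Discussion warns of limited sample size and Type II error for this comparison, but does not mention confounding.

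**The concern.** TAU is both the comparator and the platform on which the JITAIs sit. Crediting a difference in change to the JITAIs requires that the rest of treatment is comparable in the two arms. Without randomisation, this has to come from the adjustment. The adjustment as named balances sex, age and severity and leaves co-treatment alone. Nothing in the outcome model makes up for that.

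Antidepressant use is the clearest case. The article itself counts medication among the effective treatments for depression, patients on it are not excluded, and TAU is left as it is. A higher rate of use in either arm would shift that arm's average change and be absorbed by the interaction term. The error can go either way: it can produce an apparent JITAI effect or hide a real one. The only limitation stated for this comparison, Type II error, does not warn the reader of the first. At stake is the estimate passed on to the future trial.

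**Working it through.** **The plan's own figure.** The plan gives no figure on this point. Its one computed figure concerns adherence, and it reproduces. The design effect is 1 + (28 − 1) × 0.05 = 2.35, and the half-width is 1.96 × √(0.60 × 0.40 × 2.35 / (46 × 28)) = 0.041, as stated. It is not in dispute and is used here only as the source of 46 per arm (52 recruited less the 6 allowed for dropout).

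**Where co-treatment could be controlled.**

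| Step | Content in the article | Covers co-treatment? |
|---|---|---|
| Allocation | Not randomised | No |
| Eligibility | Depressive disorder, start of (C)BT, smartphone, Dutch | Therapy is required; medication is not restricted |
| Propensity score | Sex, age, severity named | Not by any named covariate |
| Outcome model | Time, group, time × group | No |
| Stated limitations | Sample size, Type II error | Confounding not named |

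**Illustrative size.** The inputs are assumptions, since the documents supply none: a factor worth 2 PHQ-9 points, a 20-percentage-point difference between arms, SD 5.5, 46 per arm, and no true JITAI effect.

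- Bias = 0.20 × 2 = 0.4 points.
- SE of the difference = 5.5 × √(2/46) = 1.147.
- Shift in z = 0.4 / 1.147 = 0.35.
- P(|Z + 0.35| > 1.96) = about 0.064, against 0.05 with no imbalance.

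**Range by simulation.** Assumptions: 52 against 52, true JITAI effect zero, logistic score, 1:1 nearest-neighbour matching, caliper 0.2 SD of the logit, 2000 replicates. The background factor is binary and unrelated to sex, age and severity.

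| Imbalance, effect of factor | Score without factor: bias, rejection, pairs | Score with factor: bias, rejection, pairs |
|---|---|---|
| 20 points, 0.3 SD | 0.07 SD, 6.4%, 40 | 0.01 SD, 4.8%, 37 |
| 20 points, 0.5 SD | 0.10 SD, 7.4%, 40 | 0.00 SD, 4.8%, 37 |
| 40 points, 0.3 SD | 0.12 SD, 8.3%, 40 | 0.01 SD, 4.0%, 30 |
| 40 points, 0.5 SD | 0.21 SD, 14.4%, 40 | 0.01 SD, 4.7%, 30 |

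The 2-point factor above is 2/5.5 = 0.36 SD, inside this range. Matching on the three named covariates leaves essentially the whole product of imbalance and effect (for example 0.4 × 0.5 = 0.20 SD). Adding the factor to the score removes it, at the price of some pairs.

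**The case against.** The strongest reply is that much of this is inferred from silence in a condensed article.

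- **The list is open.** The covariates are introduced with the word including, and a fuller list may stand in a document not shown. This is right, and the point is therefore limited to the covariates that are named.
- **Recording.** A reader might infer that medication is not recorded and so can never be adjusted for. The article does not support this. Table 2 omits medication, but it also omits sex and age, which the propensity score uses. The treatment file may hold the information as well.
- **Therapy form and therapist discipline.** A reader might count these as equally serious confounders. The Background says that behavioral activation can match full CBT and that various trained disciplines can deliver it effectively. On that account both may be weak predictors of outcome, and a factor that does not predict outcome does not confound. They deserve a balance check, not a place in the matching.
- **Mechanism.** No route to imbalance is documented. Patients and therapists come from one institution, and the treating clinicians are said to help with enrolment, not with assignment to arm. This stands: imbalance is possible, not shown. If antidepressant use follows severity, matching on severity would also remove part of any imbalance.
- **What is claimed.** The plan claims similarity only on the matched covariates. That is accurate as a statement about matching, but the third hypothesis attributes better outcomes to the JITAIs, and that needs more.
- **Status.** The distal analysis is preliminary, and progression rests on adherence and acceptability. This limits the weight of the point without answering it, because the estimates have a stated use in the next trial.

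**Conclusion.** The point holds in a limited form. As written, the plan names no covariate for background treatment in a nonrandomised comparison, and antidepressant use is the clearest gap. An imbalance in it could appear as, or conceal, a JITAI effect in the group-by-time interaction.

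The size is unknown. The illustration of 0.4 PHQ-9 points and a false-positive rate of about 6% rests entirely on the assumed 2-point effect, 20-point imbalance and SD of 5.5. The simulated range of 0.07 to 0.21 SD and 6% to 14% rests on assumed imbalances of 20 to 40 points and effects of 0.3 to 0.5 SD.

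A reader might add a second factor in the same direction and quote 0.8 points and about 11% (shift 0.8/1.147 = 0.70). The arithmetic is correct, but nothing in the article suggests two such factors acting together. Nor does the point reach the main results of the study: dose-received adherence does not depend on the TAU group, and the proximal effects are compared within participants by randomisation. This is a change worth making to a preliminary analysis, not a flaw in the trial as a whole.

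**What to change.** 1. Record antidepressant use (yes/no) at baseline in both arms, from the treatment file, and add it to the propensity model in the Distal outcomes section.
2. If too many matches are lost, put it in the outcome model instead. It should then enter with its interaction with time, because a main effect alone would not adjust the group-by-time term.
3. Record form of therapy and therapist discipline in both arms. Report their balance by arm after matching, and adjust for them in the outcome model in the same way if they are imbalanced. Do not match on them: with 52 per arm and at least five disciplines, a caliper match could lose many pairs.
4. In the Discussion, name residual confounding by co-treatment as a limitation beside Type II error.

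The cost is a few data items per participant and possibly some matched pairs. In the simulation, one added binary factor reduced about 40 pairs to 37 with a 20-point imbalance and to 30 with a 40-point imbalance. No treatment, visit or sample-size target changes.

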#### Sample size

The primary feasibility outcome is dose-received adherence, defined as the proportion of completed JITAIs among all received JITAIs during the MRT phase. A sample size calculation for this outcome was based on the precision of the estimated proportion of completed JITAIs among received JITAIs [39]. Because adherence was defined at the JITAI level, with repeated observations nested within participants, the calculation was adjusted for within-participant correlation using a design effect [40]. During the 6-week MRT phase, participants can have up to 168 decision points (42 days × 4 per day). Assuming participants are available at 66% of these moments and a probability of 25% of receiving a JITAI at a given decision point, participants are expected to receive approximately 28 JITAIs on average. Assuming an adherence proportion of 0.60, a two-sided 95% confidence interval, an average of 28 received JITAIs per participant, and a within-participant intraclass correlation of 0.05, 46 participants would yield an approximate confidence interval half-width of 0.041.

We set the recruitment target for the TAU + JITAI group at 52 participants, comprising the 46 participants indicated by the feasibility-based precision estimate plus 6 additional participants to allow for 13% dropout observed in samples with depression [41]. For consistency in the nonrandomized comparison, we will recruit an equal number of participants in the TAU group. The proximal and distal outcome analyses are intended to provide preliminary estimates to inform a future trial.

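### Caliper matching does not ensure a TAU match for every JITAI participant, and with an equal-sized TAU pool full matching is very unlikely at usual calipers

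*Protocol article*

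**What the plan says.** The Distal outcomes section under Data analyses estimates a propensity score by logistic regression on baseline covariates, "including sex, age, and severity of depressive symptoms at the start of treatment". It then matches TAU to TAU + JITAI participants by nearest neighbour with a caliper. The next sentence says what this achieves: "This method ensures that each participant in the TAU + JITAIs group has a corresponding participant in the TAU group", with a similar score. The outcome model that follows "considers the paired nature of the matched sample by including the matched pairs as random effects", which implies one-to-one matching, although the article does not say so outright.

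The group sizes are fixed elsewhere. Participants with depression gives "52 for the treatment-as-usual with the JITAIs as add-on condition (TAU + JITAIs) and 52 for the treatment-as-usual (TAU) condition". Sample size explains the TAU number: "For consistency in the nonrandomized comparison, we will recruit an equal number of participants in the TAU group". The Evaluation phase part of Procedure confirms: "Allocation to the TAU + JITAI and TAU groups is not randomized".

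The caliper width, the replacement rule and the expected number of pairs are not given. A condensed article may leave these to a fuller plan, so their absence is not the point here.

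**The concern.** The guarantee describes a property that the named method does not have. A caliper exists to refuse matches that are not close enough, so it trades retention for similarity. The text promises both.

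The equal-sized pool sharpens the problem. Matching usually works by choosing comparable controls from a larger reserve, and here there is no reserve. Without replacement, either every control is used, and nothing has been selected, or some JITAI participants are dropped.

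The distal comparison addresses the third hypothesis in Study aims and hypotheses and is meant to inform a future trial. If participants drop out through matching, the estimate describes only those JITAI participants who resemble an available TAU patient. That population is not the one the text describes. It also rests on fewer people, in a comparison whose sample size the Discussion already says may be insufficient.

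**Working it through.** **1. The plan's own figure.** Sample size takes an adherence of 0.60, 28 JITAIs per participant, an intraclass correlation of 0.05 and 46 participants.

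- Design effect: 1 + (28 − 1) × 0.05 = 2.35.
- Half-width: 1.96 × √(0.60 × 0.40 × 2.35 / (46 × 28)) = 0.041, as stated.
- Dropout: 46 × 1.13 = 52; dividing instead, 46 / 0.87 = 53. The stated 52 is close enough.

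The 52 therefore comes from precision for adherence plus dropout. Nothing is added for matching loss, and TAU is simply set equal. The article gives no number of matched pairs to reproduce.

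**2. Why matching everyone corrects nothing.** Suppose all 52 are paired one-to-one without replacement. With complete data, the mean of the 52 within-pair differences equals the TAU + JITAI mean minus the TAU mean, however the pairs are formed. The same holds for each covariate, so the imbalance after matching equals the imbalance before it. Matching can improve balance here only by dropping people.

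**3. How many would be dropped.** This needs assumptions that are not in the article. Simulation (500-1000 runs per setting) used 52 versus 52, sex, age and severity in a logistic propensity model, and the same standardized group difference on each covariate. The caliper was 0.2 SD of the logit. Mean number of JITAI participants matched (share lost):

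| Imbalance | Greedy, random order | Optimal | With replacement |
|---|---|---|---|
| 0 | 39.8 (23.5%) | 42.3 (19%) | 49.7 (4%) |
| 0.2 SD | 38.0 (27%) | 40.5 (22%) | 49.3 (5%) |
| 0.3 SD | 36.2 (30%) | 38.2 (27%) | 48.7 (6%) |
| 0.5 SD | 30.9 (41%) | 32.5 (37.5%) | 46.9 (10%) |

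Without replacement, no run in this table matched all 52. With replacement, all 52 were matched in about 5-19% of runs. If only one covariate differs by 0.5 SD, about 36 pairs remain: (52 − 36) / 52 = 31% lost. With 46 versus 46 after dropout, the loss is 20-32% at imbalances of 0 to 0.3 SD.

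**4. Sensitivity to the caliper (without replacement, imbalance 0 to 0.3 SD).**

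- 0.1 SD: about 28-38% lost.
- 0.5 SD: about 8-24% lost.
- 1.0 SD, or 0.2 on the probability scale: about 0-19% lost, and some runs match everyone.

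**5. Effect of a larger pool.** At 0.2 SD with random-order greedy matching and the same imbalances, 104 controls cut the loss to 4-9% and 156 controls to 2-4%.

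**6. Cost in precision.** In a simple two-group comparison the variance is proportional to 1/n. Going from 52 to 42.3 or 36.2 per group multiplies it by 52 / 42.3 = 1.23 or 52 / 36.2 = 1.44. For an illustrative effect of d = 0.5, power is 72% with 52 per group, 60% with 39 and 56% with 36. The effect detectable with 80% power, (1.96 + 0.84) × √(2/n), rises from 0.55 at 52 to 0.63 at 39 and 0.66 at 36. These figures ignore repeated measures and any gain from pairing, so they show relative cost only.

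**The case against.** The strongest reply is that the article fixes neither the caliper nor the replacement rule, and may leave both to a fuller plan. This stands, and it limits what can be claimed. A reader might infer that full matching is impossible, or that a quarter to a third of the sample will be discarded. The article supports neither reading. A very wide caliper can match everyone, though it then gives up much of the similarity promised in the same sentence. Matching with replacement loses only about 4-10%, though the guarantee still usually fails, and reused controls do not fit a simple matched-pair random effect. Across the settings examined, the loss runs from near 0% to over 40%.

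A reader might also infer that the propensity model wrongly leaves out baseline MHC-SF, QPR and EQ-5D. The covariate list is introduced as open, and the group-by-time model already uses each outcome's baseline value as its first time point. Adding those scores is an optional improvement, not a correction.

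Propensity matching is also an accepted method, and the alternatives have costs of their own. Overlap weighting likewise moves the estimate to a different population. That is fair, but such a method states its target population in advance and discards no one.

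Finally, the stakes are limited. Sample size calls the distal results preliminary, and the Discussion concedes a risk of Type II error. Neither mentions loss through matching, and neither makes the guarantee true.

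**Conclusion.** The statement that the method secures a similar TAU counterpart for every JITAI participant is wrong for caliper matching. With 52 against 52 in a nonrandomized comparison, full matching is very unlikely at usual calipers. If it were reached one-to-one without replacement, it would leave any imbalance as it was.

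The size rests on assumptions. With a 0.2 SD-logit caliper without replacement, about 19-30% of JITAI participants are lost at imbalances of 0 to 0.3 SD, and about 30-41% at 0.5 SD, depending on the algorithm and on how many covariates differ. The loss is smaller with wider calipers or with replacement.

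The consequence is a distal comparison on an unplanned subset, with reduced precision and no allowance for it in the sample size. It does not reach the primary feasibility outcome or the micro-randomized comparison, neither of which uses matching. The point should be corrected before analysis, but it does not threaten the study's main purpose.

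**What to change.** - Delete the sentence that guarantees a counterpart for each JITAI participant.
- Make the primary distal analysis one that keeps all participants. One option is the longitudinal outcome model adjusted for sex, age and baseline severity, with these covariates allowed to act on change (for example through covariate-by-time terms). Where the baseline score is itself a response in the model, it should not also enter as a covariate. The other option is propensity weighting with the target population stated.
- Drop the matched-pair random effect from that model and keep the participant-level one.
- Keep caliper matching as a sensitivity analysis. Give the caliper, the replacement rule and the number unmatched in each group.
- Optionally, add baseline MHC-SF, QPR and EQ-5D to the propensity model.

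If matching is to stay primary, the alternative is a larger TAU pool, which costs recruitment.

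The recommended change alters analysis wording only and needs no new data or participants. Its price is more reliance on a correctly specified outcome or weight model. If overlap weights are chosen, the estimate applies to the overlap population, and the report should say so.
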